### 5.4.3 Treatment Schedule

Patients will be added to a surgical list following enrolment and a letter will be sent to the patient with confirmation of the surgery date. Each patient will be randomised as close as possible to the time of surgery. Patients will attend for surgery typically between 4 and 8 weeks following enrolment. Surgery will occur only once, unless a patient has symptomatic cataract in both eyes, in which case the patient will return approximately 2-8 weeks later for surgery on the second eye. Surgery on the second eye will be performed according to the randomised allocation for the first eye, unless there is a specific patient preference not to do so.

### 5.4.4 Compliance and Adherence

It is not expected there will be any problems with compliance as the trial treatment is delivered on one occasion only.

Patients will be required to re-confirm their consent prior to randomisation on the day of surgery and a patient may change their mind about having surgery at this point. Investigators and staff at site should follow local procedures for ensuring informed consent for surgery has been given, and that all patients have had sufficient opportunity to ask questions about the surgery.

Patients will be required to comply with the follow up schedule, to complete postal questionnaires at 6 weeks and 6 months post-surgery, and attend clinic at 3 months and 12 months post-surgery following surgery to the study eye. Site staff will be responsible for booking these appointments and following up any patients who do not attend. No additional research visits are required for patients having surgery for both eyes.

### 5.4.5 Concomitant Care

For patients on pre-existing treatment for intraocular pressure control, or inflammatory eye disease, these will be continued as required for the treatment of the respective condition.

## 5.5 Outcomes

### 5.5.1 Primary Outcomes

*Primary outcome*

- Uncorrected distance visual acuity (UDVA, logMAR) at 3 months post-surgery in the study eye, measured using a standard ETDRS chart at a starting distance of 4 metres.

### 5.5.2 Secondary Outcomes

*Secondary outcomes (all time points relate to times after cataract surgery in the study eye)*

- Uncorrected distance visual acuity (UDVA) at 12 months following surgery on the study eye.
- Corrected distance visual acuity (logMAR) at 3 and 12 months following surgery on the study eye (ETDRS logMAR chart at a starting distance 4 metres).
- Ocular complications within 3 and 12 months of surgery on the study eye. A complication will be defined as any event that causes unintentional injury to an ocular structure, or requires additional treatment, or has a negative effect on a patient's health or eyesight.
- Uncorrected and corrected visual acuity (using the ETDRS chart at a starting distance of 4 metres) and complications in the second eye (for those with bilateral cataracts), and with both eyes open at 3 and 12 months following surgery on the study eye.
- Proportion of patients with vision within 0.5 and within 1 dioptre of intended refractive outcome (and second eye for those with bilateral cataracts) at 3 and 12 months following surgery on the study eye.
- Quality of life as measured by the EQ-5D-3L questionnaire+vision bolt-on question (EQ-5DV) at 6 weeks, 3, 6 and 12 months.
- Patient reported vision health status using Catquest-9SF (26) at 3, 6 and 12 months.
- Cost-utility analysis reported as the incremental cost-effectiveness ratio and cost-effectiveness acceptability curves.
- Corneal endothelial cell count (additional safety measure) in both eyes, at 3 and 12 months following surgery on the study eye.

## 5.6 Participant Timeline

**Figure 1: Schedule of Assessments**

|  | Standard pre-assessment (for study and non-study patients) | **Baseline** | **Randomisation** | **Follow up** | | | | |
| --- | --- | --- | --- | --- | --- | --- | --- | --- |
|  |  | Surgical Pre Assessment Visit | Randomisation and surgery | Standard non-study post-op appt | 6 weeks post-surgery (by post)  (ideally +/-14 days) | 1^st^ trial apt: 3 months post-surgery  (ideally +/-14  days) | 6 months post-surgery  (by post)  (ideally+/-14  days) | 2^nd^ trial apt: 12 months post-surgery  (ideally +/-14 days) |
| Visit Number | *1* | *1 or later* | 2 | *3* |  | *4* |  | *5* |
| Past medical and ocular history | X | X |  |  |  |  |  |  |
| Consent for cataract surgery | X |  |  |  |  |  |  |  |
| Informed Consent & eligibility screening |  | X |  |  |  |  |  |  |
| Identification of study eye |  | X |  |  |  |  |  |  |
| Visual acuity: UDVA, pinhole, +/- glasses (Snellen), each eye | X |  |  | X |  |  |  |  |
| Visual Acuity: UDVA^1^ & CDVA^2^ (logMAR) each eye and binocular |  |  |  |  |  | X |  | X |
| Visual acuity (LogMAR) with usual method of correction |  |  | X^7^ |  |  |  |  |  |
| Subjective refraction |  |  |  |  |  | X |  | X |
| Ocular biometry | X |  |  |  |  |  |  |  |
| Pentacam corneal topography | X^6^ | X |  |  |  | X |  | X |
| Optical coherence tomography (OCT)^3^ | X^6^ | X^8^ |  | X^6^ |  | X |  | X |
| Inclusion/Exclusion Criteria |  | X |  |  |  |  |  |  |
| Catquest-9SF questionnaire |  | X |  |  | X | X | X | X |
| EQ-5D-3L+vision bolt-on question (EQ-5DV) |  | X |  |  | X | X | X | X |
| CSRI^5^ |  | X |  |  |  | X | X | X |
| Endothelial cell count measurement | X^6^ | X^8^ |  |  |  | X |  | X |
| Surgery |  |  | X |  |  |  |  |  |
| Adverse Event Collection |  |  |  |  | X | X | X^4^ | X |

*^1^UDVA: uncorrected distance visual acuity. All visual acuity measures will use the standard ETDRS logMAR chart at 4 metres. At the baseline visit (usual pre-assessment clinic for cataract surgery) ETDRS will be the usual care visual acuity measure and thus can be taken prior to consent, ^2^CDVA: corrected distance visual acuity using subjective refraction result .^3^OCT will be measured as part of the standard pre-assessment for all patients. OCT will be repeated at 3 and 12 months. ^4^patient reported complications only. ^5^The Client Service Receipt Inventory (CSRI) is a questionnaire for collecting retrospective information about study patients’ use of health and social care services, accommodation and living situation, income, employment and benefits.(28) ^6^Some patients will have these tests performed at the standard pre-assessment visit, depending on the site local procedure for surgical pre-assessment. ^7^Current glasses or unaided. ^8^ baseline procedures which should be repeated if surgery is delayed for more than 3 months.*

### 5.6.1 Early Stopping of Follow-up

Participants will be followed up for 12 months following surgery on the study eye.

If a participant chooses to discontinue participation in the trial prior to surgery, they will be either listed for standard phacoemulsification cataract surgery and followed up in clinic, or discharged if they choose not to proceed with cataract surgery.

If a participant chooses to stop follow up, this view must be respected and the participant withdrawn from trial follow up. CCTU should be informed of the withdrawal in writing using the appropriate **FACT** documentation. Data already collected will be kept and included in analyses according to the intention-to-treat principle for all participants who stop follow up early. If a patient is only willing to return for one follow up visit, then this should be the 3 month visit.

### 5.6.2 Participant Transfers

If a participant moves from the area making continued follow up at their consenting centre difficult, every effort should be made to arrange for them to be followed at another participating trial centre. Written consent should be taken at the new centre and a copy of the participant’s CRFs provided to the new centre. Responsibility for the participant remains with the original consenting centre until the new consent process is complete.

### 5.6.3 Loss to Follow-up

Patients who are temporarily lost to follow up (i.e. they miss or delay one or more follow-up visits) will be able to resume their participation in the trial by keeping their remaining appointments as close as possible to the schedule defined in the protocol. All participants will be asked to provide contact details for, and consent to contact where necessary, a “best alternative contact” such as a relative or close friend.

Every effort will be made to maintain contact with all patients, however, if a patient misses the 3 and 12 month follow-up appointments and is not contactable by any means, they will be deemed to be lost to follow up.

### 5.6.4 Trial Closure

The end of the trial will be defined as when the last participating patient has attended their 12 month follow up visit, all data is complete and all data queries have been resolved.

The REC will be notified within 90 days of the end of the trial. A summary report of the research will be sent to the REC within 12 months of the end of the trial.

## 5.7 Sample Size

The primary clinical outcome is uncorrected visual acuity in the study eye on the ETDRS logMAR chart at a starting distance of 4 metres at 3 months following surgery, ascertained by an optometrist masked to the trial group. A change in visual acuity of 1 line of the chart is considered to be clinically important, one logMAR line is 5 letters (each letter is 0.02 logMAR) and the test-retest variability is reported as 0.07 logMAR. If there is truly no difference in mean logMAR between the two groups, then 432 patients (216 per group) would provide 90% power to be sure that a 95% two sided confidence interval would exclude the non-inferiority limit of 0.1 logMAR, assuming a common standard deviation (SD) of 0.32. The SD is from the Royal College of Ophthalmologists’ National Ophthalmic Database of unaided vision 3 months following cataract surgery (n= 20,155).

However, although treatment is delivered on an individual basis, each patient cannot be assumed to generate independent information since they will be clustered within surgeons. To take account of clustering by surgeon (i.e. the variation between surgeons in the treatment effect) the sample size must be increased by an inflation factor f = 1 + (m-1)*p. Assuming a total of 16 surgeons contribute and an average cluster size (m) of 50 (patients/surgeon) and an estimated ICC (p) of 0.012, this yields an f of 1.59. A total of 688 patients (344 per group) would enable the trial to take account of clustering by surgeon. To allow for an anticipated 15% dropout rate (the mean age of patients undergoing cataract surgery is 75 years old and many have significant systemic comorbidities) the total sample size required is 808 patients (404 per group). The sample size calculation was conducted using Stata/IC version 12.1 (StataCorp, College Station, TX, USA. The IDMC will be asked to review all the assumptions used for the sample size calculation before the end of recruitment.

## 5.8 Recruitment and Retention

### 5.8.1 Recruitment

We aim to recruit 808 patients in total (404 in each arm) over the 18 month recruitment period.

Patients will be recruited via NHS sites as described in section 5.1.1. Screening, recruitment and randomisation will be undertaken by qualified individuals at site, and this will be documented on the site delegation log. Individuals taking consent will have received appropriate training.

The trial will start with an internal pilot of recruitment at St Ann’s Hospital, London for the first 6 months. We expect to recruit 30 patients during the 1^st^ month and 34 patients per month thereafter. During the internal pilot phase we will identify and investigate any barriers to recruitment before opening recruitment out to additional site(s).

Screening logs, recruitment rates and dropout rates will be reviewed at monthly meetings of the Trial Management Group. Any barriers to recruitment will be investigated and mechanisms put in place to correct them. Failure to meet our target recruitment of 200 patients during the internal pilot will trigger submission of an action plan to HTA, including adding further trial site(s) if necessary, to ensure the target is met.

It is expected that St Ann’s Hospital will recruit approximately 75% of the total required, leaving the additional 25% to be recruited by additional trial site(s).

### 5.8.2 Retention

The follow up period for the FACT trial is for 12 months. Participants will be required to attend two clinic visits at 3 and 12 months and will also need to complete trial questionnaires that will be posted at 6 weeks and 6 months.

Completion and return of the questionnaires at 6 weeks and 6 months will provide a prompt for the trial team to remind the patient of their next visit. If the participant does not return the questionnaire at these visits, a member of the trial team will phone the patient to remind them to post the questionnaires or to bring them at their next visit. This contact will also be used as an additional reminder of the date of the next follow up visit.

## 5.9 Assignment of Intervention

### 5.9.1 Allocation

#### 5.9.1.1 Sequence generation

Patients will be randomised in a 1:1 ratio to either surgical procedure via the Sealed Envelope.com website. Sealed Envelope is a randomisation service provider that provides a proven, reliable and centralised randomisation system. The system will be custom designed to the trial requirements.

This will use minimisation with a random element with stratification by a) treatment centre, b) surgeon, and c) whether in the local clinician’s opinion, the patient will require surgery on one or both eyes.

A random trial arm allocation will be computer generated. Sealed Envelope will provide the randomised treatment for each participant.

#### 5.9.1.2 Allocation concealment mechanism

On the day of surgery and as close to the time of surgery as possible, delegated staff at site will enter the patient’s initials, gender, date of birth, date of consent, eligibility criteria fulfilment, centre, surgeon and whether the patient requires surgery in one or both eyes into the SealedEnvelope.com secure website, which will then allocate the randomised treatment. The treatment allocation will not be concealed to the investigator given this is not a masked trial. Usernames and passwords for Sealed Envelope will be provided to site staff during the site activation procedure.

#### 5.9.1.3 Allocation Implementation

The responsibility for enrolling and randomising participants into the trial lies with the Principal Investigator and staff at site.

Individuals at participating centres will be provided with a secure login to the sealedenvelope.com website, according to a delegation of responsibilities log. The users will be required to log into the website and answer eligibility questions before entering stratification data and being permitted to randomise. The randomisation result will be shown directly online, with an email confirmation to the user and also to the Trial Manager.

### 5.9.2 Masking

Due to the nature of the intervention, neither the trial participants nor the treating clinician will be masked to the treatment allocation.

To ensure masking of the outcomes data, visual acuity and refraction at 3 and 12 month follow up visits will be performed by a trial Optometrist who will be masked to the treatment allocation. After these measures have been completed, complications data will be collected by patient medical notes and reviewed by an unmasked delegated member of the trial team and entered on the Case Record Forms (CRFs). Each site will be responsible for putting procedures in place to ensure the Optometrist is kept masked at all times, and will remind each patient not to reveal their treatment to the trial Optometrist at these two visits.

### 5.9.3 Emergency Unmasking

As the trial participants and unmasked delegated site staff will have access to the treatment allocation, emergency unmasking will not be necessary.

## 5.10 Data Collection, Management and Analysis

### 5.10.1 Data Collection Methods

Each participant will be given a unique trial Participant Identification Number (PIN). Data will be collected at the time-points indicated in the Trial Schedule (Table 1).

Data will be collected by the trial sites using paper Case Record Forms (CRFs) and securely transferred to CCTU. The data will be entered into the database by a member of the **FACT** trial team and stored on secure servers based at UCL. Training on paper CRF completion and storage for site staff listed on the delegation of responsibilities log will be provided at the site initiation meeting(s).

Data collection, data entry and queries raised by a member of the **FACT** trial team will be conducted in line with the CCTU Standard Operating Procedure (SOP) and trial specific Data Management Plan.

Identification logs, screening logs and enrolment logs will be kept at the trial site in a locked cabinet within a secured room.

Clinical trial team members will receive trial protocol training. All data will be handled in accordance with the Data Protection Act 1998.

### 5.10.2 Data Management

Data will be entered in the approved **FACT** database by a member of the **FACT** trial team at CCTU and protected using established CCTU procedures.

Participants will be given a unique trial Participant Identification Number (PIN). Data will be entered under this identification number onto the central database stored on the servers based at CCTU. The database will be password protected and only accessible to members of the **FACT** trial team at CCTU, and auditors if requested. The servers are protected by firewalls and are patched and maintained according to best practice. The physical location of the servers is protected by CCTV and security door access.

The database and coding frames have been developed by the Clinical Trial Manager in conjunction with CCTU. The database software provides a number of features to help maintain data quality, including; maintaining an audit trail, allowing custom validations on all data, allowing users to raise data query requests, and search facilities to identify validation failure/ missing data.

After completion of the trial the database will be retained on the servers of UCL for on-going analysis of secondary outcomes.

The identification, screening and enrolment logs, linking participant identifiable data to the pseudononymised Participant Identification Number, will be held locally by the trial site. This will either be held in written form in a locked filing cabinet or electronically in password protected form on hospital computers. After completion of the trial the identification, screening and enrolment logs will be stored securely by the sites for 5 years unless otherwise advised by CCTU.

### 5.10.4 Statistical Methods

#### 5.10.4.1 Statistical Analysis Plan

The primary analysis will be conducted following the intention to treat principle where all randomised patients are analysed in their allocated group whether or not they receive their randomised treatment. Baseline characteristics will be summarised for each treatment groups. Continuous data will be summarised using means and standard deviations, if data appear Gaussian, or medians and interquartile ranges. Binary data will be reported as proportions and percentages.

All statistical tests will use a 2-sided P value of 0.05 unless otherwise specified. All confidence intervals presented will be 95% and two sided. A detailed statistical analysis plan will be developed for approval by the Trial Steering Committee and review by the Independent Data Monitoring Committee and finalised before the first substantive statistical analysis. All statistical analyses will be performed using Stata (StataCorp, College Station TX, USA).

#### 5.10.4.2 Statistical Methods – Outcomes

The primary outcome is uncorrected distance visual acuity at 3 months following surgery on the study eye, measured using an ETDRS chart at a starting distance of 4 metres. Mean UDVA will be reported together with a two-sided 95% confidence interval. This will be compared between treatment groups using regression analysis adjusting for baseline habitual logMar^[[1]](#footnote-2)^ visual acuity and the randomisation stratifiers (treatment centre, surgeon, and whether or not patients have one or both eyes eligible). We will include trial site in our regression models as a fixed effect and surgeon as a random effect. If the upper end of the 95% CI for the difference between means does not cross the non-inferiority limit of 0.1 logMAR, then laser surgery will be regarded as non-inferior. If the mean difference is negative and its 95% CI lies wholly to the left of zero, then we can conclude that laser surgery is superior to manual surgery. We will perform sequential testing of the non-inferiority and superiority hypotheses.

Secondary continuous outcomes such as uncorrected distance visual acuity at 12 months, corrected distance visual acuity and patient reported outcome measures Catquest-9SF will be analysed in a similar fashion. The percentage of study eyes experiencing adverse events (e.g. posterior capsule tears, dropped lens) in the two groups will be compared using Fisher’s exact tests.

In addition regression analyses will be performed for continuous outcomes such as corrected distance visual acuity at 12 months for the study eye, adjusting for baseline habitual logMar visual acuity and the randomisation stratifiers (treatment centre, surgeon, and whether or not patients have one or both eyes eligible). Baseline habitual logMar visual acuity is only collected for the study eye and therefore distance visual acuity outcomes for the fellow eye, whether they are unaided or corrected, will only be adjusted for the randomisation stratifiers.

Pearson’s correlation coefficients (or Spearman’s rank correlation coefficients, depending on the distribution of the data) will be used to assess the relationships between the continuous objective and subjective outcome measures.

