**Arm B: Laser assisted phacoemulsification cataract surgery**

### 5.4.1 Arm A

#### 5.4.1.1 Manual Phacoemulsification cataract surgery

Arm A is the current standard treatment.

All patients randomised to arm A will be treated with manual phacoemulsification cataract surgery.

This is the standard method of cataract surgery at participating trial sites. Typically this will involve topical or local anaesthesia (with or without concurrent sedation depending on patient preference). The eye to undergo cataract surgery will be dilated according to standard local unit practice.

All patients will be seen by a doctor or trained designated healthcare professional to ensure the appropriate surgical consents have been completed and the eye to be operated on marked (including corneal steep axis identification if required). The intraocular lens to be used will be selected from the biometry according to patient preferred refractive outcome.

Following local standard surgical checks (WHO guidelines), the patient will be transferred to the anaesthetic room or direct to the operating theatre where the intended anaesthetic is given. If a depot pellet has been used for dilation, this will be removed at this stage.

Phacoemulsification cataract surgery will then be performed according to local standard practice. This will typically involve a 2.20 – 2.75mm corneal incision, capsulorrhexis, hydrodissection, phacoemulsification, cortical clear up and intraocular lens implantation. Peri-operative antibiotics will be given again according to local standard practice. Surgeons may choose to treat corneal astigmatism by their preferred method including on axis surgery, additional corneal incisions (eg. limbal relaxing incisions or opposite clear corneal incisions); or by the use of a toric intraocular lens according to standard practice (typically >2.00 dioptres of regular corneal astigmatism). A plan for astigmatism will be made prior to randomisation. Post-operative care including post-operative eye drops will be as per standard unit practice for cataract surgery.

The surgery start time will be defined as application of antiseptic solution to the periocular region by the operating surgeon following the final patient check. The surgery end time as the removal of the surgical drape.

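### Adding age and pre-operative corneal astigmatism to the primary UDVA model would tighten the non-inferiority interval slightly at almost no cost; leaving them out is not an error

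*Protocol*

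**What the plan says.** Section 5.10.4.2 names the primary model. The outcome is UDVA in the study eye at 3 months: "This will be compared between treatment groups using regression analysis adjusting for baseline habitual logMar" acuity, plus centre, surgeon and whether one or both eyes are eligible. Site is a fixed effect and surgeon a random effect. Habitual acuity is defined in the footnotes as acuity with the usual correction: "Current glasses or unaided". Non-inferiority is judged from the resulting interval: "If the upper end of the 95% CI for the difference between means does not cross the non-inferiority limit of 0.1 logMAR". Superiority is then tested on the same interval.

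Other sections show which baseline information exists before surgery:

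- Figure 1 schedules "Pentacam corneal topography" at the baseline visit and ocular biometry at the standard pre-assessment.
- Section 5.9.1.2 lists the data entered at randomisation, including "gender, date of birth, date of consent".
- Section 5.4.1.1 requires an astigmatism plan before randomisation and leaves the method of correction to the surgeon. Toric lenses are used "typically >2.00 dioptres of regular corneal astigmatism".

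Neither age nor corneal astigmatism appears in the model or among the minimisation factors in section 5.9.1.1.

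**The concern.** The outcome is measured without spectacles, so corneal astigmatism left after surgery feeds directly into it. The eligibility criteria set no upper limit on astigmatism, and lesser degrees may remain uncorrected.

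The one clinical covariate in the model is poorly matched to this source of variation. In spectacle wearers habitual acuity largely hides refractive error, and in the others it does not. It also reflects the lens opacity that surgery removes.

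What is at stake is precision only. Any outcome variance that pre-operative astigmatism and age could explain stays in the residual, and it widens the interval that decides non-inferiority and then superiority.

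**Working it through.** **Inputs from the protocol.** Section 5.7 gives a margin of 0.1 logMAR, SD 0.32, true difference 0, cluster size 50, ICC 0.012 and 15% dropout. Section 5.10.4.1 gives the interval: "All confidence intervals presented will be 95% and two sided".

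**The plan's own figure first.** Section 5.7 states that "432 patients (216 per group) would provide 90% power".

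- Per arm: 2 × 0.32² × (1.960 + 1.282)² / 0.1² ≈ 215.2, rounded up to 216, so 432 in total. This reproduces.
- Clustering: 1 + 49 × 0.012 = 1.588. Then 216 × 1.59 = 343.4, rounded up to 344 per arm, so 688. This reproduces.
- Dropout: 688 / 0.85 = 809.4 against 808 stated, which is close enough.

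The 0.32 is a raw outcome SD, so the sample size takes no credit for any covariate.

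**Assumed inputs, not in the documents.** Loss of 0.08–0.15 logMAR per dioptre; SD of corneal astigmatism 0.6–0.8 D.

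**Variance explained at the protocol's SD.** R² = (slope × SD of astigmatism / 0.32)².

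- Low: (0.08 × 0.6 / 0.32)² = 0.150² = 2.3%.
- Middle: (0.115 × 0.7 / 0.32)² = 0.252² = 6.3%.
- High: (0.15 × 0.8 / 0.32)² = 0.375² = 14.1%.

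These are marginal values and act as ceilings, for two reasons. The slope applies to astigmatism still present after surgery, whereas the covariate is measured before surgery and some of it is then corrected. Some of the variance is also shared with covariates already in the model.

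**Effect on the interval.** Effective n per arm = 344 / 1.588 = 216.6. Residual SD = 0.32 × √(1 − R²), where R² is the share added. Half-width = 1.96 × residual SD × √(2 / 216.6). Narrowing = 1 − √(1 − R²). Power = Φ(0.1 / SE − 1.96).

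| Added R² | Half-width (logMAR) | Narrowing | Power |
|---|---|---|---|
| 0 | 0.0603 | – | 90.2% |
| 0.02 | 0.0597 | 1.0% | 90.8% |
| 0.05 | 0.0587 | 2.5% | 91.6% |
| 0.10 | 0.0572 | 5.1% | 92.9% |

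In patients, 688 / (1 − R²) − 688 gives about 14 extra evaluable patients at R² = 0.02 and 76 at R² = 0.10. The documents offer no figure for what age would add, so none is claimed.

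**Chance imbalance in astigmatism.** With SD 0.7 D and 344 per arm, the SE of the between-arm difference is 0.7 × √(2 / 344) = 0.053 D. At 0.115 logMAR per dioptre this is 0.006 logMAR, or about 0.012 at the 95% limit. The largest assumed values (0.8 D and 0.15) give about 0.018.

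**The case against.** The strongest reply is that nothing here is wrong. The model adjusts for baseline acuity and for every minimisation factor, leaving out further covariates biases nothing, and the 808 was set without credit for adjustment. All of this stands. A reader might infer from the omission that the trial is underpowered or its estimate distorted. The documents do not support that: power is about 90% with no covariate gain at all, and the ordinary interval already allows for random imbalance in astigmatism, which is small in any case.

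A reader might also infer that habitual acuity is the model's only prognostic term. It is not. Surgeon, centre and one or both eyes are included, and the protocol itself treats surgeon as prognostic through its ICC and the complication risks by grade in section 4.1. Habitual acuity is only the sole baseline clinical measurement.

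A larger gain is tempting too. An outcome SD of 0.20 with the extreme assumptions would give (0.15 × 0.8 / 0.20)² = 36%. The protocol's SD is 0.32, so that figure has no footing here. Surgical correction (section 5.4.1.1, and laser keratotomy in section 5.4.2.1) weakens the link further. Because keratotomy is among the laser steps, the slope may also differ by arm, which would reduce what a common slope gains.

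Finally, covariates are often left to the SAP. That does not dispose of the point, because section 5.10.4.2 itself states the list. It does mean that the SAP, due before the first substantive analysis, is a natural place for the change.

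**Conclusion.** The point holds as a modest, optional improvement in precision. On an assumed added R² of 2–10%, the interval narrows by about 1–5% and power rises from 90.2% to between 90.8% and 92.9%, with the lower part of the range more likely. The size rests on a slope and an astigmatism SD that the documents do not give, on the design effect of 1.588, and on using the raw SD of 0.32 as the starting point. Validity, error rates and the adequacy of the sample size are unaffected. The argument for acting is that the cost is close to nil and that the same interval also serves the superiority test, for which section 5.7 gives no power calculation.

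**What to change.** Before any comparative analysis, state in section 5.10.4.2 or the SAP that the 3- and 12-month UDVA models include age and pre-operative study-eye corneal astigmatism magnitude as fixed covariates.

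- Take astigmatism from one named pre-operative source, for example the baseline Pentacam.
- Use pre-operative values only, since post-operative astigmatism can be affected by treatment.
- Handle missing covariate values within the multiple imputation already planned in section 5.10.5.
- Keep the current model as a sensitivity analysis.

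The cost is a sentence or two of text and no new examination. One check is needed: Figure 1 schedules the topography but does not say that an astigmatism value reaches the case report form, so the trial team should confirm that it is captured or can be extracted. Timing matters, because covariates added to a non-inferiority model after comparative data have been seen would invite suspicion.
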